## 5.3 Exclusion criteria

- Less than 18 years old
- All other AO 2.3 Fractures
- Soft tissues G2, G3
- Open fractures and concomitant injuries
- Forearm fractures (except Proc. Styloideus ulnae)
- Pathological fractures
- Patients who are unable to support the postoperative treatment by themselves

## 5.4 Enrollment into the study

All patients who neet the inclusion criteria, and do not fulfill any exclusion criterion, are included ib the study (see recruiting, 5.1).

# Course of the study and methods of investigation

## 6.1 Clinical examinations

Clinical examinations will be carried out in order to confirm the diagnosis, as a control, and to evaluate the satisfaction of the patients as well as the evolution of pain.

## 6.2 Study-related

Not applicable.

## 6.3 Planned testing

Regular clinical follow-up examinations and controls as well as targeted surveys regarding pain and patient satisfaction are planned. Based on these data, both methods can be compared to each other.

## 6.4 Implementation and finalization

The participation at this study is entirely voluntary. A patient can revoke his consent to his participation in the study at any time without stating reasons. Preoperatively, appointments for reevaluation are fixed 1, 2, and 6 weeks postoperatively. Moreover, the patients should know that, after 1, 2, and 6 weeks, as well as after 6 months, he has to fill out a questionnaire and that a clinical control will take place. Only, if a patient agrees to these conditions, he can be included in the study. For those patients, which have agreed to participate in the study, closed envelopes are deposited in the operating theatre. Each envelope contains a piece of paper reading “VacoHand” or “splint”. Depending on the envelope, the patient has to wear initially the VacoHand® or the splint for 1 week in total (unless the operating surgeon indicates otherwise). Then, 1 week postoperative, the splinting is changed from the forearm splinting to the VacoHand® and vice versa.

[figure not shown]

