## 1.3 Summary of the study protocol (Synopsis)

| Study code | VACUM | |
| --- | --- | --- |
| Title of the study | Outcome analysis of the therapy of a radius fracture with  VacoHand®/ forearm splint | |
| Study design | Prospective clinical cross-over study | |
| Planned number of patients: | 50 patients | |
| Duration of the study | Planned beginning of the study:  Planned total duration of the study: | 5/2011  18 months |
| Primary endpoint | The primary endpoint of this study is the patient satisfaction, which is evaluated according to the SF-36 questionnaire. Secondary endpoints are the determination of the DASH Score and of the Neutral-0 Method for the hand as well as for the length of the period of disability. | |
| Inclusion criteria | 18 years of age and AO2.3 A2, A3, B1, B2, B3, C1, C2 fractures which need to be operated with a volar stable plate (2.4mm, 3.5mm, all types) | |
| Exclusion criteria | - Less than 18 years of age - All other AO 2.3 fractures - Open fractures and concomitant injuries - Forearm fractures (except Proc. Styloideus ulnae) - Pathological fractures - Patients, who are unable to support the postoperative treatment by themselves | |

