# 3 Goals of the study

The primary endpoint of this study is patient satisfaction, which is measured by the SF-36 questionnaire, after AO2.3 A2, A3, B1, B2, B3, C1, C2 fractures requiring surgery, with a volar angular stable plate (2.4mm, 3.5mm, all types), which are treated postoperatively with a VacoHand^®^/ splint. Targeted surveys relating to pain and the quality of life are carried out. Based on these data, both postoperative treatment methods are compared to each other. Secondary endpoints are the determination of the DASH Score and of the Neutral-0 method for the hand, as well as the duration of the period of disability. In order to achieve these goals, follow-up examinations will be carried out 1, 2, and 6 weeks as well as 6 months after the postoperative treatment.

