# Study design

## 4.1 Design

This study is a prospective clinical cross-over study

.

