## 5.2 Inclusion criteria

- At least 18 years old
- AO2.3 A2, A3, B1, B2, B3, C1, C2 fractures requiring surgery, which have been treated with a volar angular stable plate (2.4mm, 3.5mm, alle types)
- Soft tissue G0, G1
- Patients have to be able to actively support the postoperative treatment.

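### The surgeon's open-ended exception to the envelope (Protocol 6.4) lets the device order a patient receives depend on prognosis

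*Protocol*

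**What the plan says.** Section 4.1 describes the design: "This study is a prospective clinical cross-over study". Under section 6.4, for patients who have agreed to take part, "closed envelopes are deposited in the operating theatre". Inside, "Each envelope contains a piece of paper reading" one of the two device names, and that device is worn first.

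The instruction then carries an exception: the patient wears the VacoHand "or the splint for 1 week in total (unless the operating surgeon indicates otherwise"). The sentence after it has none: "Then, 1 week postoperative, the splinting is changed from the forearm splinting to the VacoHand® and vice versa".

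Section 3 sets the assessments: "follow-up examinations will be carried out 1, 2, and 6 weeks as well as 6 months after the postoperative treatment". Section 6.5, repeated in the Data management section, requires complete deletion of a patient's data after drop-out or withdrawal of consent.

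No section of the text shown gives grounds for the exception, says until when it may be used, or requires it to be written down. None says who opens the envelope or at what moment.

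**The concern.** The envelope is the only thing in the protocol that separates a patient's prognosis from the order of devices. The same sentence that gives the envelope its force also lets it be set aside, by the person who has just seen the fracture and the fixation. Eligible fractures run from A2 to C2 (section 5.2), so there is room for prognosis to influence such a decision.

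Three kinds of comparison are exposed:

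- Week 1 alone compares the two devices between different patients.
- At 6 weeks and 6 months, patients who followed the plan have had both devices, so only the two orders can be compared.
- The within-patient contrast loses patients who stay on one device. It is also biased if patients with a worse prognosis are moved and recover at a different speed between weeks 1 and 2.

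A later analysis plan cannot repair this if the draw and the departure were never recorded. The rule on departures is a matter of conduct and belongs in the protocol.

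**Working it through.** The protocol has no figure to reproduce, so the check has two parts.

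**1. The two sentences of section 6.4 side by side**

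- If the exception covers the device, a patient can receive the order that was not drawn, or stay on one device.
- If it covers only the duration, the order stands but the first period may be shorter or longer than a week. This conflicts with the unqualified switch at one week, and the week 1 and week 2 assessments then no longer line up with one week on each device.
- If it covers both, both problems arise.

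The text does not choose between these readings. Under each of them, what the patient receives can differ from what the plan assigns, and nothing requires a record.

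**2. Illustration for the device reading**

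The synopsis gives 50 patients. Everything else is assumed: 25 per order as drawn, 40% severe (10 in each order), and *k* severe patients moved from VacoHand-first to splint-first. Grouping is by order received.

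- Severe share, VacoHand-first: (10 − *k*)/(25 − *k*)
- Severe share, splint-first: (10 + *k*)/(25 + *k*)

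Let *s* be the severe-minus-other difference on an endpoint. A comparison between orders is then biased by (difference in severe shares) × *s*.

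For the crossover contrast, let τ be the device effect and π the mean change between periods (week 1 minus week 2) within an order group. The week 1 minus week 2 difference has mean τ + π(VacoHand-first) in one group and −τ + π(splint-first) in the other. Half the difference between them is τ + [π(VacoHand-first) − π(splint-first)]/2. If severe patients differ from the others by *d* in this period change, the bias is half the difference in severe shares times *d*. A period term does not remove it.

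| *k* moved | VacoHand-first severe | Splint-first severe | Bias between orders | Bias in crossover contrast |
|---|---|---|---|---|
| 0 | 10/25 = 40% | 10/25 = 40% | 0 | 0 |
| 2 | 8/23 = 35% | 12/27 = 44% | 0.10 *s* | 0.05 *d* |
| 5 | 5/20 = 25% | 15/30 = 50% | 0.25 *s* | 0.125 *d* |
| 10 | 0/15 = 0% | 20/35 = 57% | 0.57 *s* | 0.29 *d* |

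Biases are in absolute size. The last row moves every severe VacoHand-first patient and is the extreme case. Moves in the other direction mirror the table, and moves in both directions partly cancel. Grouped by the order drawn, every row returns to 40% against 40%.

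**The case against.** The strongest objection is to the reading. The parenthesis follows the words on one week in total, and the English reads as a translation, so it may concern wearing time only. In that case no patient changes order and the table does not apply. This stands as a real ambiguity. It does not remove the point, because the duration reading still conflicts with the fixed switch and still leaves departures unrecorded.

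It can also be said that the table is a one-directional assumed case which vanishes under analysis by the order drawn, and that such an analysis rule may sit in an analysis plan not shown. That is correct. However, such an analysis needs a record of what was drawn, which the protocol does not require, and data on drop-outs, which the protocol deletes.

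A reader might infer more than the text supports:

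- *That the surgeon holds or can reach the envelopes.* The protocol places them in the operating theatre and does not say who opens them. Opening an envelope in theatre after consent is not a fault in itself.
- *That missing detail on numbering or opacity is an error.* On its own it is only unstated detail.
- *That departures will follow severity.* The protocol does not say so. The eligibility criteria already narrow the range by excluding C3, soft tissue G2 and G3, open fractures and concomitant injuries.
- *That eligibility is contradictory.* The synopsis has "fractures which need to be operated with a volar stable plate" and section 5.2 has "which have been treated with a volar angular stable plate". This is a difference of tense, and nothing indicates that envelopes are opened too early.
- *That a stated randomisation is broken.* The text shown never says that the order is randomised. It supports only that the order received may depart from the order drawn.

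**Conclusion.** The point holds in a limited form. Section 6.4 states an open-ended exception to the envelope's assignment, leaves its scope unclear, and sets it beside a fixed switch at one week that allows for no exception. Followed as written, it can let prognosis shape the order received.

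The size cannot be determined, since the protocol gives no rate, direction or reason for departures. The 25% against 50% in the illustration rests on assumed group sizes, an assumed severe share, five moves all in one direction, and grouping by order received. It shows that a few departures could matter in a study of 50, not that this will happen. The effect on the crossover contrast further requires that severe fractures change at a different speed between weeks 1 and 2. No view is taken on when a clinical departure is right.

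**What to change.** Changes to the protocol:

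1. State whether the exception covers the device, the duration or both, and reconcile it with the fixed switch at one week.
2. Have the surgeon confirm, before the envelope is opened, that the patient is eligible and suitable for either device. Do not allocate the patient otherwise.
3. Open envelopes in a pre-generated random order, and log date and time. If the order is blocked, use varying block sizes: with a known total of 25 per order in an unblinded single-clinic study, the last allocations could be predicted.
4. Record every departure, with its reason and the device worn.
5. Analyse allocated patients by the order drawn.
6. Reconcile item 5 with the deletion of drop-out data in section 6.5 and the Data management section. In particular, say whether a patient who departs from the envelope counts as a drop-out.

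The cost is protocol wording, preparation of the envelopes and one log sheet. A few patients, in a number the protocol gives no basis to estimate, would be screened out before allocation.

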# 2 Introduction

## 2.1 Summary

The distal radius fracture is one of the most common disease patterns in trauma surgery with an incidence of two to three per 1,000 inhabitants. It is a distal fracture of the radius. As it is located close to the wrist, it is commonly referred to as a broken wrist. It occurs in all age groups, but mostly between 6 and 18 years and between 60 and 70 years. The formation mechanism is triggered by a traumatic fall on the extended (Colles fracture), or, more rarely, on the bent wrist (Smith fracture). In children, the distal radius fracture occurs mainly during sports. In adults, however, it is mainly caused by tripping and falling the on uneven or slippery ground. The goal of every therapy, either conservative or operative, is the anatomical reconstruction of the joint surface. Unstable extraarticular and intraarticular fractures are mostly stabilized by plate osteosyntheses, which are mostly fixed to the flexor side, rarely also to the extensor side of the radius close to the wrist. The main advantage of plating is the immediate practice safety, so that the physiotherapy can be started shortly after the postoperative application of the cast,. An early mobilisation can prevent the negative consequences of joint immobilization, like e.g. muscular atrophies, joint immobilisation, tendon conglutination, and capsule contraction. Several studies have demonstrated that the immobilisation provokes a considerable degree of muscular atrophy, especially during the first two weeks. Moreover, it causes metabolic, neurological, and functional adaptations, so that the muscular strength may decrease by half after 4-6 weeks of immobilisation in the cast. A possible solution for this problem is the use of a dynamic vacuum orthesis: It provides the stability of a circular forearm splint, and which therefore allows for an early low-risk increase of load, as well as for a limited mobility in the wrist. Furthermore, the comfort of the patients is increased by the fact that an othesis is less heavy than a splint and can be easily applied by the patient himself after having received an instruction. This enables a regular body care. Besides, the limited mobility of the wrist allows for establishing a more physiological functional image. Moreover, a favourable progress of the postoperative phase could reduce the period of disability in the workforce.

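### After the switch at 1 week no group has used one device only, so the 6-week, 6-month and disability results compare device sequences, not the two devices

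*Protocol*

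**What the plan says.** Section 4.1 declares the design: "This study is a prospective clinical cross-over study". Section 6.4 gives the schedule. By envelope, "the patient has to wear initially the VacoHand® or the splint for 1 week in total (unless the operating surgeon indicates otherwise"), and afterwards "Then, 1 week postoperative, the splinting is changed from the forearm splinting to the VacoHand® and vice versa". No washout is described, and the text gives no end for the second period.

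Assessments continue well past the switch. Section 6.4 tells the patient that "after 1, 2, and 6 weeks, as well as after 6 months, he has to fill out a questionnaire", with a clinical control at the same times. Section 3 ties all four visits to the study goals: "follow-up examinations will be carried out 1, 2, and 6 weeks as well as 6 months after the postoperative treatment".

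On the purpose of the data, Section 3 states: "Based on these data, both postoperative treatment methods are compared to each other". Its secondary endpoints are DASH, Neutral-0 "as well as the duration of the period of disability". Section 6.3 repeats that the examinations and surveys allow the two methods to be compared. The synopsis lists the same endpoints without time points. The introduction (Section 2.1) gives one reason for interest in late outcomes: "a favourable progress of the postoperative phase could reduce the period of disability in the workforce".

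**The concern.** A device comparison needs groups, or periods within patients, that differ in the device. After the switch the groups still differ in which device came first, but each has used both. An outcome measured at 6 weeks or 6 months, or a duration that runs past week 1, reflects the whole sequence. It cannot be divided between VacoHand and splint.

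The protocol nevertheless describes its data as comparing the methods and sets no limit by visit. A difference at 6 months, or in time off work, could therefore be reported as an effect of one device, and the absence of a difference as an absence of device effect. Neither conclusion would follow. The primary endpoint is exposed as well, because the SF-36 has no named time point in the synopsis or Section 3.

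**Working it through.** **Inputs.** There are two sequences with a first period of 1 week (Section 6.4). Visits are at 1, 2 and 6 weeks and 6 months (Sections 3 and 6.4), counted here from surgery as in Section 6.4. The length of the second period, L weeks, is not in the text. I assume L = 1 and L = 5 (worn to week 6) as an illustrative range. The protocol states no figure to reproduce.

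**Exposure by visit.** By week t the second device has been worn for m = min(t − 1, L) weeks. The VacoHand-first group has 1 week of VacoHand and m of splint; the splint-first group has the reverse. The difference in VacoHand weeks is 1 − m.

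| Visit | VacoHand first (VacoHand/splint weeks) | Splint first (VacoHand/splint weeks) | Difference in VacoHand weeks |
| --- | --- | --- | --- |
| Week 1 | 1/0 | 0/1 | 1 − 0 = 1 |
| Week 2 | 1/1 | 1/1 | 1 − 1 = 0 |
| Week 6 and 6 months, L = 1 | 1/1 | 1/1 | 1 − 1 = 0 |
| Week 6 and 6 months, L = 5 | 1/5 | 5/1 | 1 − 5 = −4 |

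For any L above 0, m is above 0 at week 6, so both sequences contain both devices. This holds whatever the missing figure shows about L.

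**What weeks 1 and 2 estimate.** Let τ be the effect of VacoHand minus splint while worn, and λ the difference in carry-over from week 1 into week 2. Contrasts are VacoHand first minus splint first. Healing common to both groups cancels within each visit.

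- Week 1: τ.
- Week 2: −τ + λ.
- Cross-over estimate: [τ − (−τ + λ)]/2 = τ − λ/2.

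Week 1 alone is a clean comparison between groups. Weeks 1 and 2 together estimate τ if carry-over is equal (λ = 0).

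**What a late visit estimates.** As an illustration, assume that wearing VacoHand rather than splint in week k adds δ_k to the late outcome.

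- Sequence contrast: δ_1 − (δ_2 + … + δ_(1+L)).
- One device throughout: δ_1 + δ_2 + … + δ_(1+L).

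These agree only if the effects after week 1 sum to zero. With all δ equal, L = 1 gives δ − δ = 0, against 2δ for sustained use; L = 5 gives δ − 5δ = −4δ, against 6δ.

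**Period of disability.** Let it last D weeks from surgery (the starting point is my assumption). If D ≤ 1, it falls under one device. If D > 1, the first device covers 1/D of it: 50% for D = 2 and 17% for D = 6 (illustrative values). There is one value per patient, so the second period has no value of its own to set against the first.

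**The case against.** The best case for the plan has four parts.

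- **Section 3 does not attach the comparison to every endpoint at every visit.** The comparison sentence directly follows the one on surveys of pain and quality of life, and the secondary endpoints come after it. This stands: a device claim at 6 months is not stated in so many words. But all four visits are tied to the goals and no sentence limits the comparison to early ones.
- **Late results are not only about order.** If the second device is worn longer, the groups differ in how long they wore each device, by up to 4 weeks in the range above. This also stands, and a reader who infers that late results reflect order alone goes too far. The wear difference is still tied to order and leaves no single-device group.
- **The rationale is partly short-term.** Section 2.1 mentions strength loss over 4–6 weeks in a cast, but also atrophy mainly in the first two weeks, comfort and body care. A 1-week period can address such aims, and the effect of the initial device on later outcome is a legitimate question. It is, however, a question about sequence.
- **Time points can be left to a statistical analysis plan.** True of the choice of visit. But no analysis can recover a late device contrast that the switching schedule does not create.

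A reader might also infer that late results read by envelope label will have the wrong sign, or that a null result will be called equivalence. The documents support neither: the length of the second period is unknown, and the protocol makes no equivalence claim.

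**Conclusion.** The point holds for the 6-week and 6-month results and for any disability period longer than 1 week. They compare envelope-assigned sequences: order alone if the devices are worn equally long, order mixed with unequal wear if not. Over the assumed range of 1 to 5 weeks for the second period, the difference in VacoHand wear at week 6 runs from 0 to 4 weeks.

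The conclusion rests on the schedule in Section 6.4 being followed. The surgeon's exception means that some patients may depart from it, so it should not be said that every patient switches at 1 week. It does not rest on the sample size: with 50 patients and no stated allocation ratio, a detectable difference would need further assumptions and would not bear on what is being compared.

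A reader might infer that the secondary endpoints cannot address the devices at all. That is too strong. DASH and Neutral-0, if recorded at weeks 1 and 2, can inform the device comparison, as can the SF-36. For week 2 this assumes that the second device is still worn then.

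**What to change.** In the synopsis and Section 3:

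1. Base the VacoHand-versus-splint comparison of SF-36, DASH and Neutral-0 on the week-1 assessment (between groups) and on weeks 1 and 2 together, analysed as a two-period cross-over with a period effect. Note that no washout is described and that carry-over cannot be excluded.
2. Label the week-6 and 6-month results and the period of disability as comparisons of sequence (VacoHand first versus splint first) that do not by themselves support a conclusion about either device.
3. Bring the comparison sentence in Section 6.3 into line.

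The change is to wording only, with no change to visits or data collected. Its price is giving up a late device claim, including one on disability, that this design cannot support. How long each device is worn is a clinical matter, and no change to it is proposed.

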## 6.5 Data protection

The patient data are registered and stored in a database at the Clinic for Trauma and Restorative Surgery, BG Klinik Tübingen. The deletion of the data, which are related to the study, is scheduled to take place in 10 years. Only the principal investigator and the authors of this study as well as research associates which have been selected by the authors of the study are authorized to access these data. The data will only be shared only in a pseudonymized fashion, if necessary. In case of a drop out or of the revocation of the permission by the patient, the data will be completely deleted. For the publications resulting from this project, only pseudomynized data will be used.

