# Information on statistics, data analysis

Data analysis will be carried out at the Institute for Clinical Epidemology and Applied Biometry of the University of Tübingen.

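### Drop-out alone, without revoked permission, triggers full deletion of a patient's data, which cannot be undone and may bias the device comparison

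*Protocol*

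**What the plan says.** The rule stands in section 6.5 (Data protection) and again, in the same words, under Data management: "In case of a drop out or of the revocation of the permission by the patient, the data will be completely deleted". It names two triggers joined by an or, so either suffices. It makes no exception for data already collected, the allocated order of devices, the device worn at exit or the reason for leaving. The protocol does not define drop-out.

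The rule operates in this setting:

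- Design (4.1): "This study is a prospective clinical cross-over study".
- Switch of device (6.4): "Then, 1 week postoperative, the splinting is changed from the forearm splinting to the VacoHand® and vice versa".
- Follow-up (section 3): "follow-up examinations will be carried out 1, 2, and 6 weeks as well as 6 months after the postoperative treatment".
- Endpoint (section 3): "The primary endpoint of this study is patient satisfaction, which is measured by the SF-36 questionnaire".
- Leaving the study (6.4): "A patient can revoke his consent to his participation in the study at any time without stating reasons".
- Sample size (synopsis, 1.3): 50 patients, with no drop-out rate stated.
- Statistics section: "Data analysis will be carried out at the Institute for Clinical Epidemology and Applied Biometry of the University of Tübingen". It gives nothing further on the handling of patients who leave.

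**The concern.** Deleting data when a patient withdraws permission is a data-protection matter and is not disputed here. The fault is that the same erasure applies to a patient who merely drops out and has not asked for it.

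Three things are at stake. First, outcome data may be lost after they have done their work: a patient with questionnaires on both devices who disappears before the 6-month visit can be removed entirely. Second, the endpoint is satisfaction, and dissatisfaction with a device is a plausible reason to leave. If leaving depends on the outcome, the patients who remain are a selected group and the device comparison may be biased. Third, any harm or reason for leaving recorded for that patient can be erased too.

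This is not a detail to be left to a statistical analysis plan. Such a plan can define analysis sets and missing-data methods, but it cannot use records that have been destroyed.

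**Working it through.** **Reading the text.** The two sections agree, so this is the operative rule and not a slip in one place. Section 6.4 deals with revocation of consent separately, and the deletion rule lists drop-out beside revocation, so drop-out without revocation is covered.

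**Timing.** The switch is at 1 week and questionnaires fall at 1, 2 and 6 weeks and 6 months. A patient seen at weeks 1 and 2 and lost afterwards has been observed on both devices. If classed as a drop-out, that patient loses both observations.

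**No plan figure to reproduce.** The protocol states 50 patients without alpha, power, effect size, SD or drop-out rate. What follows is illustration under assumptions that are not in the documents.

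*Precision.* For a paired comparison at two-sided 5% and 80% power, the detectable difference in SDs of the within-patient difference is (1.960 + 0.842)/√n:

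- n = 50: 2.802/√50 = 0.396
- n = 45 (10% deleted): 2.802/√45 = 0.418
- n = 40 (20% deleted): 2.802/√40 = 0.443

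The loss of precision is modest.

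*Bias.* Assume no true device difference, SD 10 on each device, within-patient correlation ρ, and that the fraction d of patients scoring lowest on one device leave and are deleted. With φ the standard normal density and z_d its d-quantile, the mean paired difference among those left shifts by

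shift = 10 × (1 − ρ) × φ(z_d)/(1 − d).

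For d = 0.10, φ(z_d) = 0.1755 and 0.1755/0.90 = 0.195. The shift is 10 × 0.7 × 0.195 = 1.37 points at ρ = 0.3 and 10 × 0.3 × 0.195 = 0.58 at ρ = 0.7. A simulation of 2,000,000 patients gave the same values.

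The type I error then follows from shift × √n / SD of the difference among those left. At d = 0.10, ρ = 0.3: 1.37 × √45 / 11.22 = 0.82, so the error is Φ(−1.96 + 0.82) + Φ(−1.96 − 0.82) ≈ 0.130.

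| Deleted | n left | Shift, ρ = 0.7 to 0.3 (points) | Type I error (nominal 5%) |
|---|---|---|---|
| 5% | 48 | 0.32 to 0.76 | 6.0% to 7.4% |
| 10% | 45 | 0.58 to 1.37 | 8.1% to 13.0% |
| 20% | 40 | 1.06 to 2.45 | 14.5% to 29.4% |

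Under this mechanism the shift favours the device on which the leavers scored low. Enrolling 56 patients to finish with 50 after 10% loss (50/0.90 = 55.6) would restore precision but leave the bias.

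The table compares those left with everyone having been observed on both devices. Keeping the data would recover all of that for patients lost after both periods, and only part of it for those lost sooner.

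**The case against.** The strongest reply is that the effect is uncertain and possibly small. The documents give no drop-out rate, mechanism or reasons, the simulated mechanism is extreme, and at 5% deletion the error rate barely moves. That stands: bias is possible, and its size and direction are unknown.

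Several stronger readings are tempting and should be resisted.

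- *Only completers can be analysed.* Because drop-out is undefined, the text does not say that a missed visit or a rejected device counts. Section 6.4 also lets the surgeon depart from the envelope without calling that patient a drop-out. What is excluded is whoever is classed as a drop-out.
- *The count of drop-outs is erased.* The rule concerns patient data. Nothing forbids an anonymous tally; the protocol is simply silent on one.
- *The week-1 versus week-2 contrast is the primary comparison.* The protocol names no primary time point.
- *A patient who leaves in the first week is a lost comparison.* The first postoperative questionnaire is at 1 week. Someone who leaves before it has no outcome on either device, so deletion costs the reason and any harm, but no within-patient contrast.
- *The bias equals the shift in one sequence's mean.* With an assumed 25 per sequence and leavers 1 SD low, deleting 3 shifts that mean by 3/22 = 0.14 SD and deleting 5 by 5/20 = 0.25 SD. In a cross-over, a level shift common to both periods cancels within patients and the bias is zero. If instead the leavers' device difference is 1 SD off in one sequence only, the effect averages two sequences and the shift halves, to about 0.07 and 0.125 SD.

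None of this touches the core. Drop-out alone triggers an erasure that cannot be reversed. The missing definition makes matters worse, because someone must decide case by case whose data are destroyed.

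**Conclusion.** The concern holds in this form: the protocol orders full deletion after drop-out even when permission has not been revoked. Confidence in the text is high. Two consequences follow from the text. Data already recorded on both devices can be lost for a patient who leaves late, and an analysis of all allocated patients becomes impossible once any drop-out has been deleted.

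Bias in the device comparison is a possibility, not a demonstrated result. The figures of 0.6 to 1.4 points and 8 to 13% type I error at 10% deletion, or 6 to 7% at 5%, rest wholly on assumed values: no true difference, SD 10, correlation 0.3 to 0.7, and exit by the lowest scorers on one device. A reader might infer that the comparison will be tilted towards the less tolerated device; the documents do not support that as fact. The rule should be changed before any deletion takes place, because the loss is permanent.

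**What to change.** Change section 6.5 and Data management together:

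1. Remove drop-out as a trigger, so that deletion follows only from revocation of permission. How revocation itself is handled can stay as it is.
2. Define drop-out, and say how it differs from a missed visit, a departure from the allocated device and a revocation.
3. Keep all data collected up to drop-out and analyse them in the sequence to which the patient was allocated.
4. Record the time of exit, the device worn at exit and any reason the patient volunteers. No reason may be required, in keeping with section 6.4.
5. Keep an anonymous count of exits by allocated sequence, including exits by revocation.
6. Align the consent form (Appendix 3).

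The cost is an ethics amendment and revised consent wording, with no extra patients or visits. Patients already promised deletion must be handled under their existing consent. Data of patients who revoke will still be missing, so the analysis would cover all allocated patients less those.
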